# Efficacy and safety of combined treatment of miniscalpel acupuncture and non-steroidal anti-inflammatory drugs: an assessor-blinded randomized controlled pilot study

**DOI:** 10.1186/s13063-017-2418-1

**Published:** 2018-01-12

**Keywords:** Miniscalpel acupuncture, Chronic neck pain, Pilot study, Non-steroidal anti-inflammatory drugs

## Abstract

**Background:**

Chronic neck pain is a common musculoskeletal disease during the lifespan of an individual. With an increase in dependence on computer technology, the prevalence of chronic neck pain is expected to rise and this can lead to socioeconomic problems. We have designed the current pilot study to evaluate the efficacy and safety of miniscalpel acupuncture treatment combined with non-steroidal anti-inflammatory drugs (NSAIDs) in patients with chronic neck pain.

**Methods:**

This seven-week clinical trial has been designed as an assessor-blinded, randomized controlled trial with three parallel arms. Thirty-six patients will be recruited and randomly allocated to three treatment groups: miniscalpel acupuncture treatment; NSAIDs; and miniscalpel acupuncture treatment combined with NSAIDs. Patients in the miniscalpel acupuncture and combined treatment groups will receive three sessions of miniscalpel acupuncture over a three-week period. Patients in the NSAIDs and combined treatment groups will receive zaltoprofen (one oral tablet, three times a day for three weeks). Primary and secondary outcomes will be measured at weeks 0 (baseline), 1, 2, 3 (primary end point), and 7 (four weeks after treatment completion) using the visual analogue scale and the Neck Disability Index, EuroQol 5-dimension questionnaire, and Patients’ Global Impression of Change scale, respectively. Adverse events will also be recorded.

**Discussion:**

This pilot study will provide a basic foundation for a future large-scale trial as well as information about the feasibility of miniscalpel acupuncture treatment combined with NSAIDs for chronic neck pain.

**Trial registration:**

Korean Clinical Research Information Service registry, KCT0002258. Registered on 9 March 2017.

**Electronic supplementary material:**

The online version of this article (doi:10.1186/s13063-017-2418-1) contains supplementary material, which is available to authorized users.

## Background

Chronic neck pain (CNP) is a common musculoskeletal disease with a lifetime prevalence of up to 67% [1]. According to a previous study, the one-year prevalence of neck pain was 29% and 40% for men and women, respectively [2]. In Korea, the lifetime prevalence of CNP is 20.8% [3]. With an increase in dependence on computer and smart phone technology, the prevalence rate of CNP will continue to rise. Pain can be directly related to substantial medicine consumption, absenteeism from work, unemployment, and disability [4, 5]. Therefore, symptom relief is important to improve the quality of life.

Medication, massage, exercise, physiotherapy, and patient education are common methods for the management of CNP [6]. However, the effects of these conventional therapies are limited and the validity of many CNP treatment guidelines is unclear [6, 7]. Although pain-control drugs such as non-steroidal anti-inflammatory drugs (NSAIDs) are one of the most commonly used drugs for CNP, their long-term use carries a risk of side effects and intolerance [8]. Modalities from the field of complementary and alternative medicine (CAM) are also frequently used for treatment [9]. These include acupuncture, herbal medicine, cupping, moxibustion, and pharmacopuncture [10]. Patients with chronic musculoskeletal disease tend to utilize both conventional and CAM treatments for more positive outcomes [11].

Miniscalpel acupuncture (MA) tends to exert better therapeutic effects on chronic musculoskeletal pain compared with regular acupuncture treatment [12]. MA combines Traditional Chinese Medicine meridian theory and modern surgical principles and it requires an understanding of anatomical structures. The aim of MA is recovery of the kinetic state of soft tissue through peeling adhesion and removal of attached tissues [13], with the advantage of quicker recovery and pain reduction compared with regular acupuncture [14]. Furthermore, it shows superior and long-lasting effects compared with regular acupuncture [15].

Although CAM and conventional treatment modalities are frequently applied in combination, their efficacy and safety have rarely been investigated in clinical trials. In this pilot study, we will investigate the efficacy and safety of MA combined with NSAIDs in patients with CNP. The results will provide clinical evidence for evaluating the feasibility of large-scale randomized controlled trials (RCTs) of this combination treatment for CNP.

## Methods/Design

### Design

The protocol of this assessor-blinded RCT follows the Declaration of Helsinki and Korean Good Clinical Practice. The study will be conducted at Daegu Oriental Hospital of Daegu Haany University, Daegu, Republic of Korea. Independent researchers blinded to randomization will assess the outcomes and analyze statistics. Informed consent to participate in the clinical trial will be obtained after the researcher provides sufficient information and explanations regarding the study interventions. This protocol follows the SPIRIT guidelines and the checklist and figure are available at the end of the manuscript.

This study is designed as a pilot trial to calculate the appropriate sample size for further RCTs. Each group will include 12 participants, allowing for a 20% dropout rate for evaluating the pragmatic purpose of this trial. A total number of 36 participants will be included, which is larger than the minimum number recommended for pilot studies (Additional files 1 and 2).

### Participants

One of the main objectives of this study is to provide an estimate of the sample size required for the full-scale clinical RCT. In total, 36 participants with CNP will be recruited through advertisements in local newspapers, on hospital websites, and on bulletin boards. If individuals are interested in participating, they will be invited to the hospital for a screening visit. Eligibility will be determined by one researcher on the basis of the results of physical and radiographic assessments. After completing the screening questionnaire, participants will be guided through the informed consent process. They will be informed about randomization to any one of three treatment groups: MA; NSAIDs; and combined treatment groups. Written informed consent will be obtained from each participant before the initiation of any treatment. After consent forms are obtained, participants will be randomly allocated to one of the three groups in a 1:1:1 ratio (Fig. 1).

**Fig. 1 Fig1:**
[figure not shown]
*Flow chart* of our pilot randomized controlled trial

### Eligibility criteria

Individuals aged 19–75 years who agree to participate after providing written informed consent will be selected as study volunteers. The inclusion criteria are as follows: men or women aged 19–75 years; symptoms such as neck pain and stiffness lasting for ≥ three months; a baseline score of ≥ 4 on the visual analog scale (VAS) for pain; and provision of written informed consent.

Exclusion criteria are as follows: individuals with abnormalities in neurological functions such as cervical nerve function, deep tendon reflexes, and muscle and sensory functions; those with serious sensory or motor disorders requiring surgical treatment; those with a history of spinal surgery or those with procedures scheduled during the study; those with spinal disorders, including vertebral fracture, spinal infection, inflammatory spondylitis, and malignancy, on computed tomography or magnetic resonance imaging; those who are pregnant, planning pregnancy, breast feeding, or refusing to consume certain forms of contraceptives; those with other chronic diseases that can affect the outcomes of the study interventions, including cardiovascular disease, diabetic neuropathy, active hepatitis, fibromyalgia, rheumatoid arthritis, dementia, and epilepsy; those with other severe musculoskeletal problems in areas other than the neck; those with serious psychiatric or psychological disorders; those using aspirin or anticoagulant medications; those using NSAIDs; those with abnormal findings in blood tests for renal or hepatic function; and those deemed ineligible by the recruiting researcher.

### Randomization and allocation concealment

The 36 patients will be randomized using simple randomized procedures, with a 1:1:1 allocation ratio. Written informed consent will be obtained before randomization. Random numbers will be generated by an independent statistics professional using SPSS version 19.0 for Windows (release 19.0 K; SPSS Inc. Armonk, NY, USA). Sealed opaque assignment envelopes will be used for allocation concealment. The participants will be allocated into the predefined treatment arms. Allocation concealment will not be broken until study completion. The treatment arm and random number of an individual participant will be recorded in the case report form and randomization table. Outcome assessors and data analysts will be blinded to interventions.

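### Simple randomisation of 36 patients rarely yields the stated 12 per group: exact balance has probability about 2.3%, and the smallest arm averages 9.1

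*Protocol article*

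**What the plan says.** Under Randomization and allocation concealment, the protocol article names the method: "The 36 patients will be randomized using simple randomized procedures, with a 1:1:1 allocation ratio". The same section says how the sequence is made: "Random numbers will be generated by an independent statistics professional using SPSS version 19.0 for Windows". Assignments go into sealed opaque envelopes. The Participants section repeats that "participants will be randomly allocated to one of the three groups in a 1:1:1 ratio".

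The Design section gives the group size as fixed: "Each group will include 12 participants, allowing for a 20% dropout rate for evaluating the pragmatic purpose of this trial". It adds that "A total number of 36 participants will be included, which is larger than the minimum number recommended for pilot studies". No section mentions blocks, strata or a list holding a set number of each treatment.

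**The concern.** Simple randomisation is the standard term for assigning each patient independently, without restriction on the totals. The ratio 1:1:1 then describes the probabilities, not the counts. A group size stated as 12 needs a restricted scheme, and none is named. This is not detail left to a fuller document: the article names its method, and that method does not fit the group size it gives.

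The per-arm size matters here because it is the main planning figure. The article gives no effect size, standard deviation, power or required number of evaluable patients. It gives 12 per group with a 20% dropout allowance, and a total said to exceed a pilot minimum. The Design and Participants sections make sizing the full-scale trial a main purpose, and the Discussion adds its effect size. An arm that comes out small gives weaker estimates for exactly that purpose.

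**Working it through.** **Inputs.** 36 patients, three arms, 1:1:1 and simple randomisation (Randomization and allocation concealment); 12 per group and 20% dropout (Design).

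**The plan's own figures.** 3 × 12 = 36, so the total agrees with the group size. With 20% dropout, 12 × 0.8 = 9.6 completers per group. The article gives no evaluable number to compare with this.

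**Chance of exact balance.** Under independent assignment with probability 1/3 per arm, the arm sizes are multinomial:

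P(12, 12, 12) = 36! / (12!³ × 3³⁶) = 0.0226, or 2.3%.

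**Size of one given arm.** It is binomial with mean 36 × 1/3 = 12 and SD √(36 × 1/3 × 2/3) = 2.83. Then 12 ± 1.96 × 2.83 runs from 6.5 to 17.5, so one arm will usually have 7 to 17 patients; the exact binomial probability of that range is 95.0%.

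**Smallest arm and spread.** Summing the multinomial probabilities over every split of 36 gives:

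| Quantity | Value |
|---|---|
| Mean smallest arm | 9.12 |
| Mean largest arm | 14.97 |
| Mean gap, largest minus smallest | 5.85 |
| P(smallest arm ≤ 9) | 54.3% |
| P(smallest arm ≤ 8) | 31.2% |
| P(smallest arm ≤ 7) | 15.4% |
| P(all arms between 11 and 13) | 14.7% |

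An arm of 9 with 20% dropout leaves 9 × 0.8 = 7.2 completers, against 9.6 from an arm of 12.

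**Precision of a pairwise contrast.** The variance is proportional to 1/n₁ + 1/n₂. Balanced, this is 2/12 = 0.1667. Averaged over all splits under simple randomisation, it is 0.1776. The ratio is 0.1776 / 0.1667 = 1.066, about 6.6% more variance.

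A single 9/12/15 split shows how the loss is spread, relative to balance:
- 9 v 12: (1/9 + 1/12) / (1/6) = 1.167
- 9 v 15: (1/9 + 1/15) / (1/6) = 1.067
- 12 v 15: (1/12 + 1/15) / (1/6) = 0.900

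The mean of the three is 1.044.

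**Check of possible remedies.** Blocks of 3 and 6 drawn freely with equal chance do not guarantee balance at patient 36. A block boundary falls there with probability about 2/3. Otherwise a block of 6 is cut in half, and its first three places hold one of each arm with probability (2 × 2 × 2)/20 = 0.4. So P(12/12/12) = 2/3 + 1/3 × 0.4 = 0.80.

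For predictability, suppose that staff know all past allocations and always guess the least-used arm. In 20,000 simulated lists per scheme, the mean number of correct guesses out of 36 was 12.0 for simple randomisation, 16.1 for one shuffled list of 12 per arm, and 20.7 for freely drawn blocks of 3 and 6.

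**The case against.** The strongest reply is that the authors may use the word simple loosely, for an unblocked shuffle of a fixed list with 12 of each arm. That would give 12/12/12 every time, and it fits the randomisation table and envelopes that the article mentions. This reading is possible, but the article does not state it. It would replace one misdescription with another, since such a list is a restricted scheme.

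The second reply is that little is lost. Simple randomisation is a valid method, unequal arms cause no bias, and analysis of variance accepts unequal groups. The total of 36, which is the figure set against the pilot minimum, does not change. All of this stands, and it limits the weight of the point.

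The third reply is that restriction has its own cost. The article says that outcome assessors and data analysts are blinded; those giving the treatment cannot be. The simulation shows that small blocks are the easiest scheme to guess. This also stands, and it bears on the choice of remedy. How far it matters is unknown, because the article does not say whether recruiting staff know earlier allocations.

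A reader might infer that equal groups are impossible under the stated method, or that the comparisons will be biased. Neither follows: a 12/12/12 split is rare rather than impossible, and chance inequality in numbers affects precision only. Nor is the 17% variance increase for 9 v 12 typical. It is the worst contrast of one illustrative split, and 12 v 15 in that split gains 10%.

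**Conclusion.** The concern holds as an inconsistency between the stated method and the stated group size. Read in its standard sense, the method gives the stated size about 2.3% of the time, with a mean smallest arm of 9.1 and a 54% chance that some arm has 9 or fewer. The average cost is about 6.6% more variance per pairwise contrast, with no bias.

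These figures assume independent assignment with probability 1/3 per arm and exactly 36 patients randomised. If a fixed list of 12 per arm was in fact shuffled, the arm sizes are right and only the description is wrong.

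The point is worth correcting because the repair is cheap and the arm-level estimates feed the full trial. It does not threaten the validity of the pilot.

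**What to change.** - **Name a restricted scheme.** In Randomization and allocation concealment, replace simple randomisation with a 1:1:1 list that totals exactly 12 per arm. One option is permuted blocks of varying, undisclosed size constrained to sum to 36. The same independent statistician generates it and the sealed opaque envelopes stay.
- **Limit predictability.** Larger blocks, or one shuffled list of 12 per arm, reduce what unblinded staff can guess compared with small blocks. Without the constraint to 36, freely drawn blocks of 3 and 6 balance in only about 80% of lists.
- **Respect the timing.** Trial status says that the trial began in March 2017 and that recruitment is ongoing. The article should therefore state the method actually used. Any change to the remaining envelopes should be documented and reported as an amendment, by the route in Data monitoring. It cannot undo imbalance that has already arisen.
- **If simple randomisation is kept,** restate 12 per group in Design as an expected number, with a likely range of about 7 to 17 for any one arm.

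The cost is a corrected sentence or two and, if the scheme changes, a new list and an amendment. No extra patients are needed. The one downside of restriction is some added predictability to unblinded staff.

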### Interventions

The MA group will receive MA three times over three weeks. The NSAIDs group will be prescribed zaltoprofen 80 mg/Tab (Soleton, CJ Health Care Co., Ltd, Seoul, Republic of Korea) at a dose of one tablet administered orally three times per day over three weeks. The combined treatment group will receive MA and Soleton over three weeks. The prescription will be administered in every visit and drugs that have not been taken will be withdrawn. During the study period, all other interventions such as moxibustion and physical therapy, surgical procedures, and injections for neck pain will be prohibited. Other medications that do not influence neck pain will be allowed. Any change will be recorded at every visit.

### MA

The MA points will be as follows [16]: upper site of GV16 (insertion of nuchal ligament, origin of trapezius muscle); GB20; GB12; GV15; BL10; GV14; C4 spinous process (origin of semispinalis capitis); C5 spinous process (origin of semispinalis capitis); and C6 spinous process (origin of semispinalis capitis). A total of 12 sites that appeal to pain will be selected for treatment. The sites can be increased to a maximum of 20 according to the participant’s condition: transverse process of C1 (origin of levator scapulae); transverse process of C2 (origin of levator scapulae and medial scalene); lamina of C5 (2 cm side of spinous process); lamina of C6 (2 cm side of spinous process); and GB21 (Fig. 2). A sterilized, disposable miniscalpel (DongBang Acupuncture Inc., Republic of Korea; 0.5 × 50 mm) will be used. MA will be performed by Korean medical doctors (KMD) licensed by the Ministry of Health and Welfare. The KMD will wear a sterile mask and surgical gloves. After sterile skin preparation, participants will be administered MA at a depth of tendon or ligament level. After treatment completion, the KMD will check for any abnormality and bleeding.

**Fig. 2 Fig2:**
[figure not shown]
Miniscalpel acupuncture points: (1) below external occipital protuberance, insertion of nuchal ligament, origin of trapezius muscle, upper site of GV16; (2) 2–25.cm side down of external occipital protuberance, rectus capitis posterior major, obliquus capitis superior, GB20; (3) 4–4.5 cm side down of external occipital protuberance, GB12; (4) C2 spinous process, origin of semispinalis capitis, obliquus capitis inferior, rectus capitis posterior major, GV12; (5) side of C2 spinous process, facet joint, BL10; (6) C4 spinous process, origin of semispinalis capitis; (7) C5 spinous process, origin of semispinalis capitis; (8) C6 spinous process, origin of semispinalis capitis; (9) C7 spinous process, GV14; (**a**) transverse process of atlas, origin of levator scapulae, obliquus capitis superior, obliquus capitis inferior; (**b**) transverse process of axis, origin of levator scapulae, medial scalene; (c) lamina of C5 (2 cm side of C5 spinous process), splenius capitis, semispinalis capitis; (d) lamina of C6 (2 cm side of C6 spinous process), splenius capitis, semispinalis capitis; (e) GB21, upper trapezius

### Outcomes

The primary outcome will be measured using VAS. Changes in VAS scores after three weeks of treatment will be measured relative to the baseline scores and will be considered the primary outcome. The secondary outcome will be determined by the Neck Disability Index (NDI), EuroQol 5-dimension (EQ-5D) questionnaire, and Patient Global Impression of Change (PGIC) scale. Outcomes will be measured at weeks 0 (baseline), 1, 2, 3 (primary end point), and 7 (four weeks after treatment completion). Outcome measurements will be recorded by two independent researchers. Table 1 shows the treatment and outcome measurement schedules.

**Table 1 Tab1:** Treatment and outcome measurement schedules during our pilot study

Outcome measures	Screening	Week 0 (baseline)	Week 1	Week 2	Week 3	Week 7
Screening test	V					
Sociodemographic characteristics	V					
Randomization		V				
Laboratory test	V				V	
MA treatment		V	V	V		
NSAIDs prescription		V	V	V		
Visual analog scale	V	V	V	V	V	V
Neck Disability Index		V	V	V	V	V
EQ-5D questionnaire		V	V	V	V	V
PGIC scale			V	V	V	V
Adverse events		V	V	V	V	V
Credibility assessment					V	
Total safety assessment					V	

*NSAIDs* nonsteroidal anti-inflammatory drugs, *EQ-5D* EuroQol 5-dimension, *PGIC* Patient’s Global Impression of Change

### Primary outcome measurement

VAS is a 10-cm measurement instrument to determine the severity of pain. A 10-cm horizontal line will be used. The individuals rate his or her pain on a scale of 0–10, where 0 indicates the absence of pain and 10 indicates the worst pain imaginable. Participants will estimate their level of pain by marking on the line. Then the distance from “absence of pain” point will be measured [17, 18]. In this study, the VAS score will indicate pain at the point of measurement. Changes in VAS scores after three weeks of treatment, relative to the baseline scores, will be considered the primary outcome.

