### Secondary outcome measurement

#### VAS for pain intensity

Pain intensity will be assessed using a 10-cm VAS. Participants will be asked to report the intensity of pain at weeks 0 (baseline), 1, 2, 3, and 7.

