### Statistical analysis

The results of this study will provide a preliminary report regarding the efficacy and safety of MA treatment combined with NSAIDs for CNP. All statistical analyses will be performed using IBM SPSS version 19.0 for Windows (Release 19.0 K; IBM SPS Inc., Armonk, NY, USA) and will be based on the Statistics Guidelines for Clinical Trials [22]. The significance level of the tests will be set at 0.05. One-way analysis of variance (ANOVA) and descriptive analysis will be performed to compare baseline characteristics between groups. Trends over time and time-by-treatment interactions will be explored using repeated measures ANOVA. The Chi-square test or Fisher’s exact test will be performed to compare differences in ratios caused by AEs between groups.

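### Two VAS readings are scheduled before treatment, but the stated primary outcome is a raw change from one of them; a baseline-adjusted week-3 comparison using both would probably be more precise

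*Protocol article*

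**What the plan says.** All references are to the protocol article.

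- **Primary outcome measurement** defines the endpoint: "Changes in VAS scores after three weeks of treatment, relative to the baseline scores, will be considered the primary outcome". It also says what the scale captures: "In this study, the VAS score will indicate pain at the point of measurement".
- **Outcomes, Table 1**: the row "Visual analog scale" is ticked in all six columns, from screening to week 7. Randomization and the first treatment are in the week-0 column. Two readings are therefore planned before treatment.
- **VAS for pain intensity** lists the outcome readings: "Participants will be asked to report the intensity of pain at weeks 0 (baseline), 1, 2, 3, and 7". Screening is not among them, and week 0 carries the baseline label, as it does in the Outcomes section.
- **Eligibility criteria** require "a baseline score of ≥ 4 on the visual analog scale (VAS) for pain". The text does not say whether the screening or the week-0 reading decides entry.
- **Statistical analysis** says: "Trends over time and time-by-treatment interactions will be explored using repeated measures ANOVA". It names no baseline covariate and no use of the screening VAS.
- **Design** gives 12 participants per group, 36 in all, with a 20% dropout allowance, and says the pilot is meant to size later trials.

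**The concern.** A single rating of momentary pain carries visit-to-visit noise. In a raw change score, all the noise in the week-0 mark passes into the primary outcome. An analysis that adjusts for baseline takes over only the part of the baseline that predicts week 3, and a second pre-treatment reading can improve that prediction. The reading is already scheduled for every patient.

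Two things are at stake. With about ten completers per arm, the between-arm intervals will be wide, so any cheap gain in precision matters. The pilot's variance estimate is also meant to feed the sample size of a full trial, so an inefficient estimator would be carried forward.

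**Working it through.** **Inputs from the article.** Three arms of 12 give 3 × 12 = 36. With 20% dropout, 36 × 0.8 = 28.8, or about 29 completers. The article states no VAS variance and derives no sample size from an effect size, so there is no figure of its own to reproduce.

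**Assumptions (not in the documents).** Equal SD at all visits, with variances in units of σ². Correlations are r₀₃ (week 0 with week 3), rₛ₃ (screening with week 3) and rₛ₀ (screening with week 0). A common value r means that all three are equal.

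**Step 1. Formulas under a common r.**
- Raw change from week 0: 2(1 − r)
- ANCOVA on week 0: 1 − r²
- ANCOVA on week 0 and screening: 1 − 2r²/(1 + r)

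| r | Raw change | ANCOVA, week 0 | ANCOVA, both | Cut, week 0 vs raw | Cut, both vs raw | Added by screening |
|---|---|---|---|---|---|---|
| 0.3 | 1.40 | 0.910 | 0.862 | 35% | 38% | 5% |
| 0.5 | 1.00 | 0.750 | 0.667 | 25% | 33% | 11% |
| 0.7 | 0.60 | 0.510 | 0.424 | 15% | 29% | 17% |

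The last column compares the two ANCOVAs. Adjusting for week 0 alone supplies 35 of 38, 25 of 33 and 15 of 29 percentage points.

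**Step 2. Small-sample cost.** With k covariates and ν = 29 − 3 = 26, the expected variance of an adjusted contrast is inflated by 1 + k/(ν − k − 1).
- One covariate: 1 + 1/24 = 1.042, about 4%.
- Two covariates: 1 + 2/23 = 1.087, about 9%.
- The second covariate alone: 1.087/1.042 = 1.043, about 4%.

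Net cut of the two-covariate ANCOVA against the raw change:
- r = 0.3: 1 − 0.862 × 1.087/1.40 = 33%
- r = 0.5: 1 − 0.667 × 1.087/1.00 = 28%
- r = 0.7: 1 − 0.424 × 1.087/0.60 = 23%

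Net addition from the screening value: 1 − 0.947 × 1.043 = 1%, 1 − 0.889 × 1.043 = 7% and 1 − 0.830 × 1.043 = 13%.

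**Step 3. Correlation that decays with time.** The residual variance with both covariates is 1 − (r₀₃² + rₛ₃² − 2r₀₃rₛ₃rₛ₀)/(1 − rₛ₀²).
- rₛ₀ = 0.8, r₀₃ = 0.5, rₛ₃ = 0.4: 1 − 0.09/0.36 = 0.75, against 1.00 for the raw change. The cut is 25%.
- rₛ₀ = 0.7, r₀₃ = 0.7, rₛ₃ = 0.49: 1 − 0.2499/0.51 = 0.51, against 0.60. The cut is 15%.

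In both cases ANCOVA on week 0 alone gives the same residual (0.75 and 0.51), so the screening value adds nothing. After the 9% cost the cuts are 1 − 0.75 × 1.087 = 18% and 1 − 0.51 × 1.087/0.60 = 8%.

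**Step 4. Averaging the two readings instead.** The variance of week 3 minus the mean of the two is 1 + (1 + rₛ₀)/2 − r₀₃ − rₛ₃.
- Common r: 1.5(1 − r), a 25% cut for any r.
- r₀₃ = rₛ₃ = 0.5 with rₛ₀ = 0.7, 0.8, 0.9: 0.85, 0.90, 0.95 against 1.00. The cut is 15%, 10%, 5%.
- rₛ₀ = 0.8, r₀₃ = 0.5, rₛ₃ = 0.4: 1.00 against 1.00. No gain.
- rₛ₀ = r₀₃ = 0.7, rₛ₃ = 0.49: 0.66 against 0.60. Variance rises by 10%.

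**Step 5. Entry cut at VAS 4.** Simulation with the cut applied at screening, at week 0 or at both (mean 5 or 6 cm, SD 1.5 or 2 cm, common r of 0.5 or 0.7) put the gain from a two-reading mean over week 0 alone, as the adjusting covariate, at about 7% to 17%. If the cut falls on the screening reading alone, an averaged baseline adds 0.04 to 0.25 cm of regression to the mean to the within-arm change, where week 0 alone shows none.

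**The case against.** The strongest case against is that nothing here is wrong. Week 0 is the randomization and first-treatment visit, the article uses it consistently as baseline, and the screening VAS has an evident purpose in the entry criterion. Covariates are often left to an analysis plan, which is not shown and may already deal with this. The Statistical analysis section names repeated measures ANOVA, not a change-score test. The SD of change from week 0 is a valid input for sizing a later trial. Eligibility is judged by one researcher, while outcomes are recorded by two independent researchers, so the two readings may not be taken under the same conditions. The article also does not say whether the screening rating comes before consent.

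Most of this stands, and it limits the point to an efficiency choice. It does not remove it. The article itself fixes the primary outcome as a raw change. A repeated measures ANOVA with week 0 among its visits and no covariate contrasts the arms on that same raw change. Different measurement conditions would weaken the screening value as a predictor without biasing the comparison.

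A reader might infer more: that averaging the two readings cuts variance by a quarter at no cost, so that 36 patients do the work of 36/0.75 = 48. The documents do not support this. The quarter requires equal variances and one common correlation, and it is measured against an unadjusted change. Other plausible patterns give 0% to 15%, and strong decay gives an increase. There is also a cost in degrees of freedom. Nor is the between-arm comparison biased as planned, or the plan contradictory.

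**Conclusion.** The point holds as a cheap improvement in precision. The article schedules two pre-treatment VAS readings, defines the primary outcome as a raw change from one, and states no baseline adjustment. Given equal SDs and a common correlation of 0.3 to 0.7, a two-covariate ANCOVA reduces residual variance by 38% to 29% before small-sample cost, and by about 33% to 23% after it. In the two decay patterns examined, the reduction is 15% to 25% before cost and 8% to 18% after it. Most of the benefit comes from adjusting for week 0. The screening value contributes 5% to 17% before its own 4% cost at best, and possibly nothing.

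There is a limit. If the screening value adds nothing, the net variance ratio is 1.087 × (1 + r₀₃)/2, which reaches 1 at r₀₃ = 0.84. Above that correlation the two-covariate model would cost slightly more than it gains. All these figures rest on assumed correlations. The between-arm contrast is unbiased either way, because both readings precede treatment.

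**What to change.** Before the data analysts are unblinded, state that the arms are compared on week-3 VAS by ANCOVA, with week-0 VAS and screening VAS as separate covariates. Do not use the mean of the two as the baseline. The stated endpoint need not change: with week 0 in the model, analysing week 3 or the change from week 0 gives the same between-arm estimate. Keep the raw change from week 0 as a descriptive figure for each arm. Say which reading decides the VAS entry criterion. Report the SD at each visit, the correlations among screening, week 0 and week 3, and the ANCOVA residual SD.

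The cost is a sentence or two of wording and two degrees of freedom with about 29 expected completers. If the full trial is sized on this residual SD, it must collect both readings and use the same estimator. The reported correlations will show whether the screening reading is worth keeping there.
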